### Sample size estimation

G *Power (v. 3.1) was used to estimate the sample size needed to test hypotheses 1, 2, 3 and 5. A mixed model using treatment as a between-subjects factor (MBHC, MBHC-VR, and WL) and time as a within-subjects factor (pre, inter, post, and follow-up) will be tested. Interaction effect was powered. The sample size was estimated taking as a reference a small difference in perceived stress between MBHC with vs without VR-assisted meditation in university students [5]. With an alpha criterion of .05 and a small effect size (Cohen’s d^2^ = .08), to achieve a minimum of 80% power, a minimum sample size of 174 participants will be needed. Assuming an attrition rate, based on complete dropout of approximately 20% [5], the final sample needed will include at least 210 university students (i.e., 70 participants in each of three groups).

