Core components of MBHC include: a) paying attention to the present moment; b) cultivating acceptance and openness to the present experience, without resistance and judgment; c) developing and strengthening prosocial qualities, such as kindness and compassion; d) enhancing deep self-inquiry by examining subjective experience of thoughts, feelings, and sensations; and e) promoting healthy habits and occupations. We will also include person-centered facilitation techniques, which include: 1) Unconditional positive regard; 2) Empathy; 3) Authenticity in interactions; 4) Client-centered focus; 5) Non-directive approach; 6) Self-actualisation; 7) Reflection and clarification; 8) Non-judgmental listening; 9) Holistic approach; and 10) Emphasis on the “Here and Now”; [42] and non-violent communication practices (Observation of the situation, Recognition of feelings, Identification of needs, Formulation of clear requests) [43] to support a conducive learning environment and facilitate communication. All sessions will include mindful movement, formal and informal meditation practices, sharing personal experiences and thoughts, and exercises to do at home. At the end of each session, participants will receive a set of pre-recorded audio files and printed material to support their daily practices. The structure of the MBHC program sessions is included in *S1 Appendix*. Additionally, as an example, the material of the first session is available on the web page of the B+D+b Occupational Research Group of the Miguel Hernández University.

MBHC and MBHC-VR programs will be conducted by two instructors, both with over 25 years of experience in Tibetan, Theravada and Zen meditation; experience in retreats of weeks and months in the West and Sri Lanka, and with more than 15 and 8 years of experience, respectively, facilitating mindfulness-based programs. The program has been previously implemented at Miguel Hernández University of Elche since 2016, involving university students.

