#### Waiting list control group (WL)

Participants in the WL control group will not receive any intervention during the study. However, for ethical reasons, at the end of the 3-month follow-up assessment, participants of this WL control group will be invited to participate in the MBHC program free of charge.

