### Data analysis

#### Quantitative data analysis plan

The data analysis plan will be conducted following four steps. R Software [66] will be used for all data cleaning and statistical tests with a significance level of alpha < .05.

*Data preprocessing*. Demographics and clinical records will be described at baseline by means of frequencies (percentages) or means (SD). Independent *t*-test for continuous data and chi-square test (*χ*^2^) for categorical data will be conducted to confirm that there were no demographic or clinical differences between groups at baseline. Following the CONSORT guidelines [38], Intention-To-Treat analysis will be performed using Maximum Likelihood estimation via Expectation Maximization imputation [67]. The procedure suggested by Hair et al [68] will be followed to handle missing data: 1) the types of missing data and percentage of missing will be analyzed to ensure that none exceed the recommended thresholds; 2) Little’s MCAR (Missing Completely At Random) test will be used to assess whether the missing data is completely random; and 3) sensitivity analysis will be performed to determine the impact of missing data on the results of a study, comparing the main outcomes between completers and imputed values.

*Multilevel Modelling (MLM)*. First, efficacy of MBHC and MBHC-VR compared to WL control condition will be analyzed by using MLM. Multilevel analysis enables the control of variance associated with random factors without the need for data aggregation. Variance across participants, instructor of each group, and subgroup of delivery (i.e., edition) will be modeled as random effects. Group (i.e., MBHC, MBHC-VR, and WL) and time (i.e., pre-intervention, inter-session, post-intervention, and 3-month follow-up) will be modeled as fixed effects. Analyses will be conducted via restricted maximum likelihood estimation (REML), which provides a less biased estimate of variance components with small sample sizes [69]. The group x time interaction will be used to study the trajectories of each group throughout the intervention and to determine whether the between-group differences are maintained over time.

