P-values will be obtained through likelihood ratio tests comparing the full model (including the effect in question) with the model that excludes this effect. Z-values will be obtained to test the significance for fixed effects (estimates and standard errors data in the tables). Trends of the longitudinal data will be studied by testing the linear trend of the model for all the outcomes. Interaction effects between time and predictors will be performed. To estimate the magnitude of between-group differences at post-intervention and 3-month follow-up, effect sizes (Cohen’s *d*) will be calculated by dividing the differences in means by the pooled standard deviation (SD). The Cohen convention was used to interpret effect sizes, where effect sizes of 0.20 are categorized as small, effect sizes of 0.50 are classified as medium, and effect sizes greater than or equal to 0.80 are considered large.

Model comparison approach will follow Bliese and Ployhart [70] and Bliese [71] guidelines. The process begins by examining the nature of the outcome. To test the significance of person effects, a likelihood ratio test will be conducted to compare the null multilevel model (i.e., unconditional model) with a null single-level model, testing the null hypothesis that there are no group differences. The second step involves estimating the intraclass correlation coefficient (ICC) to calculate the between/within variation ratio. Model fit will be assessed using chi-square tests on the log-likelihood values and the Akaike’s information criterion (AIC) [72] relative goodness of fit index. According to the change in these fit indexes, the model with the last significant change will be chosen for each analysis.

MLM will be performed using the lme4 R package [73]. P-values of the lme4 outputs will be obtained by the lmerTest R package [74]. The Intraclass Correlation Coefficient (ICC) will be calculated by the sjstats R package [75]. Graphic data processing will be performed by the ggplot2 R package [76]. Visual inspection of q-q plots by the car R package [77] will reveal any deviations from homoscedasticity or normality in the dependent variables. In order to calculate multiple comparisons, Tukey/Bonferroni correction tests will be performed.

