In this study, special attention is also paid to the possibility of adverse effects associated with the practice of meditation, as evidenced by previous studies [64, 88, 89]. In anticipation of this, the participants will communicate to the research team any difficulty or symptomatology that may arise, in order to attend to and solve these events as quickly as possible and, if necessary, refer the participant to the specialized psychological services available at the university. Likewise, participants will also report possible adverse effects during and/or after VR exposure. In the MBHC-VR group of this research, VR with neutral and pleasant contents will be used in all sessions for a time between 10 and 15 minutes, favoring adaptation to the exposure and minimizing possible adverse effects.

It is also worth mentioning that the programs will be implemented by a multidisciplinary professional group with extensive experience in university education and highly qualified in MBIs. In this sense, the team is made up of occupational therapists, psychologists, physiotherapists, mindfulness experts and university professors’ experts in teaching and research.

In terms of feasibility, face-to-face interventions will be carried out in groups of about 15 people, who can be attended simultaneously, thus being a low-cost community mindfulness program for university students. If the MBHC programs designed for this study are effective, one of the advantages is that their applicability can be extended to other universities. Also, the materials and procedures will be available to the educational and scientific community. Thus, the range of effective interventions available to address university students’ mental health will be expanded.

The present trial can also contribute to expanding knowledge on personalized treatments. Baseline characteristics of individuals have started to be used as predictive factors of differential response to intervention strategies. This study will allow identifying individuals within the included sample that will benefit more from utilizing one condition relative to the other. It will also allow to establish moderating mechanisms of efficacy.

In short, and from the point of view of clinical practice, it is expected that with the proposed intervention university students will learn to relate in a healthier way with their mental processes, so as to improve their OB and their psychological well-being.

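### The random effects as described do not secure the group-by-time test against class effects that arise after baseline in the active arms, and the sample size allows for none; the size depends on an ICC the article does not give

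*Protocol article*

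**What the plan says.** Under Randomization, allocation and blinding, students are allocated individually, 1:1:1, after the baseline assessment. Teaching is in classes: the Discussion says "face-to-face interventions will be carried out in groups of about 15 people", and the MBHC section says "MBHC and MBHC-VR programs will be conducted by two instructors". The waiting list is not taught: "Participants in the WL control group will not receive any intervention during the study".

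The Quantitative data analysis plan fixes the random part of the model: "Variance across participants, instructor of each group, and subgroup of delivery (i.e., edition) will be modeled as random effects". It does not say whether these are intercepts or effects that vary with time, or whether an edition is a single class or a delivery wave containing all arms. It then gives a general rule based on change in fit: "the model with the last significant change will be chosen for each analysis". P-values are to come from likelihood ratio tests, z-values are to be used for fixed effects, and lmerTest is named as a further source of p-values.

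The Sample size estimation section treats participants as independent: "Interaction effect was powered", and "to achieve a minimum of 80% power, a minimum sample size of 174 participants will be needed". No ICC or design effect appears anywhere in the article.

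**The concern.** With individual randomisation the future classes have the same expected mean at baseline. They can differ only once teaching has begun, through the instructor, the group dynamic or the timetable. Such a difference looks like a change over time shared by classmates. The group-by-time test is a test of change, so its standard error has to carry the class-to-class variation in change. The random effects listed secure that only if a class term varies with time and stays in the model, and the article commits to neither.

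The comparison most exposed is MBHC-VR versus MBHC, the article's main objective and its Hypothesis 4. It sets four or five classes against four or five. If class variation in change is left out of the standard error, a difference between a few classes can be reported as a benefit of virtual reality more often than the nominal 5%. The stated 80% power is also too high if classmates are correlated.

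**Working it through.** **Inputs from the article.** Alpha .05; three arms; four occasions; 174 evaluable (58 per arm) and 210 randomised (70 per arm); classes of about 15; two instructors; no classes on the waiting list. At 70 per arm, 70/15 = 4.7, so four to five classes per active arm and eight to ten in all.

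**Assumed, because the article does not give them.** Class ICC after baseline of .01 to .05; within-person correlation rho of .5 or .7; 12 to 15 analysed per class.

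**1. The plan's own figure.** For a within-between interaction, df1 = (3−1)(4−1) = 6, df2 = (174−3)×3 = 513 and λ = f²·N·m/(1−rho). With f = .10, m = 4 and rho = .5, λ = .01×174×4/.5 = 13.92, which is .08×174. Power is 80.4%, and 174 is the smallest N divisible by three that reaches 80%. The stated size therefore reproduces with no clustering term.

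**2. What each reading of the random effects does.**
- *Time-constant intercepts.* An intercept for edition or instructor adds the same amount to every occasion. In post minus pre it subtracts out, so in balanced data it leaves the test unchanged.
- *Time-varying class effects, subject to the model-choice rule.* In simulation, a class effect on change was significant, and so kept, in about 3% of trials at ICC .02 and 10% at ICC .05. Type I error stayed at about 7–9% and 10–13%.
- *Edition as a wave shared by the arms.* The class is then not in the model.
- *Time-varying class effects, always kept.* Likelihood ratio tests gave about 5–6% at ICC .02 and 6–8% at ICC .05. A t test on class means stayed at about 5–6%.

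**3. Type I error of MBHC-VR versus MBHC change with class left out.** Set the outcome variance to 1. The variance of change is 2(1−rho), and the class share of it is ICC/[2(1−rho)]. The design effect is DE = 1 + (m−1) × that share, with m now the class size, and true rejection is P(|Z| > 1.96/√DE). With 58/4 = 14.5 per class:

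| rho | ICC | share of change | DE | 1.96/√DE | type I error |
|---|---|---|---|---|---|
| .5 | 0 | 0 | 1 | 1.96 | 5.0% |
| .5 | .01 | .010 | 1.135 | 1.840 | 6.6% |
| .5 | .02 | .020 | 1.270 | 1.739 | 8.2% |
| .5 | .05 | .050 | 1.675 | 1.514 | 13.0% |
| .7 | .01 | .017 | 1.225 | 1.771 | 7.7% |
| .7 | .02 | .033 | 1.450 | 1.628 | 10.4% |
| .7 | .05 | .083 | 2.125 | 1.345 | 17.9% |

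With 12 per class and ICC .05, DE is 1.55 at rho .5 (11.5%) and 1.917 at rho .7 (15.7%). Simulation with five classes of 12 per arm and rho .5 gave 7.2%, 8.4% and 11.6% at ICC .01, .02 and .05, against 4.5–5.6% for a t test on class means.

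**4. The overall three-arm test.** With an unclustered waiting list, participant and class intercepts, and a class effect that persists from post to follow-up, the simulated likelihood ratio test at rho .5 rejected in 6.5–7% (ICC .01), 8% (.02) and 12–13% (.05) of null trials. If class effects at post and follow-up are independent, the figures are 8–10% at ICC .01 and 19–31% at ICC .05, over rho .5 to .7.

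**5. Power with clustering in the active arms only.** Approximate effective N = 58 + 116/DE, with DE = 1 + 13.5×ICC:
- ICC .01: 58 + 116/1.135 = 160.2, λ = 12.82, power 76%.
- ICC .02: 58 + 116/1.270 = 149.3, λ = 11.95, power 73%.
- ICC .05: 58 + 116/1.675 = 127.3, λ = 10.18, power 64%.

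**The case against.** The strongest reply is that the plan does not ignore clustering: it names instructor and edition as random effects without condition. An article commonly leaves the choice between intercepts and time-varying terms to the full analysis plan, and an always-retained class effect on change would bring type I error to about 5–8%. That stands to this extent: it cannot be said that the authors have chosen intercepts. But the article does fix the random factors, the model-choice rule and the tests, and among the readings those words allow only an always-retained class-by-time term largely protects the test.

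Other parts of the reply also stand:
- The model-choice sentence is general and names neither edition nor instructor. That it would remove them is an inference.
- If edition is a wave, waiting-list students have an edition. Only instructor is certainly undefined for them.
- The readings in step 2 are alternatives and their effects do not add up. Under the intercept reading, the weak instructor variance hardly touches the group-by-time test.
- Dropping group-by-time after a non-significant test does not bias that test.

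A reader might infer that the plan has a type I error of 7–12% as a fixed property. It does not: the article gives no ICC, at ICC 0 the error is nominal, and other assumptions push it well above 12%. A reader might also apply the design effect to all 174 participants, which at 12 per class gives 75%, 70% and 58% power. That clusters a waiting list that has no classes and overstates the loss.

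**Conclusion.** The point holds in conditional form. As worded, the random-effects plan does not secure the group-by-time test against post-baseline class effects in the active arms. Separately, a variance estimated from two instructors rests on one degree of freedom, and that factor has no value for a third of the sample.

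The size is an assumption throughout. For ICC .01 to .05 and a persistent class effect, type I error for MBHC-VR versus MBHC change is about 7–12% at rho .5 (13% with 14 to 15 per class) and reaches about 15–18% at rho .7 and ICC .05. Power at 174 is about 76% to 64% over the same ICC range, where the article states 80%. This should be corrected before analysis. It does not show that the trial's conclusions will be wrong.

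**What to change.** - Enter instructor as a fixed effect within the two active arms.
- Define the class of about 15 as the clustering unit and say how it relates to edition. Pre-specify a random effect for each class that applies only in the active arms and only after baseline (partially nested class-by-time), with each waiting-list student standing alone.
- Keep this term and group-by-time in every model whatever their significance, and exempt both from the model-choice rule.
- Base p-values on Satterthwaite degrees of freedom through lmerTest, which the article already names, or on class-level inference, in place of z-values and likelihood ratio tests.
- State an assumed ICC in the sample size section, with its range, and restate the power it gives at the planned size. No extra enrolment is asked for.

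The cost is analysis wording, a record of each student's class, wider intervals (above all for MBHC-VR versus MBHC) and a lower stated power.

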### Hypotheses

We hypothesized that, compared to the waiting list control group, both MBHC and MBHC-VR will improve occupational indicators (Hypothesis 1), mental health (Hypothesis 2), and psychological functioning (Hypothesis 3). We expect that, compared to MBHC, MBHC-VR will have higher adherence to home practice [5], and result in greater magnitude of change in the occupational balance, mental health and psychological functioning variables (Hypothesis 4). Furthermore, we expect that improvements will be maintained at 3-months post-intervention completion [5] (Hypothesis 5). Finally, we predict that psychological functioning variables will act as mechanisms of change of occupational balance and mental health indicators in experimental vs control condition [35] (Hypothesis 6). All hypotheses will be tested in the post-training assessment, except for hypothesis 5, which will be tested in the follow-up.

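### Hypotheses 1 to 4 are set at the post-training assessment, but the test stated, and powered for H1 to H3, is the whole group × time effect over all occasions; no listed test is tied to the post-training contrast

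*Protocol article*

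**What the plan says.** Under Hypotheses, the claim against the waiting list is that "both MBHC and MBHC-VR will improve occupational indicators (Hypothesis 1), mental health (Hypothesis 2), and psychological functioning (Hypothesis 3"). The same section fixes the time point: "All hypotheses will be tested in the post-training assessment, except for hypothesis 5, which will be tested in the follow-up". H4 adds that MBHC-VR changes outcomes more than MBHC.

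Sample size estimation covers H1, H2, H3 and H5 with one mixed model, in which treatment is the between-subjects factor and "time as a within-subjects factor (pre, inter, post, and follow-up) will be tested". It then states "Interaction effect was powered".

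The Quantitative data analysis plan fits group, time and their interaction, and names several inferential procedures:
- Likelihood ratio tests: "P-values will be obtained through likelihood ratio tests comparing the full model (including the effect in question) with the model that excludes this effect".
- Z-values for the individual fixed effects.
- A trend test: "Trends of the longitudinal data will be studied by testing the linear trend of the model for all the outcomes".
- Tukey/Bonferroni multiple comparisons, without saying which comparisons are meant.

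The between-group difference at post-intervention is named only for Cohen's d, which is an estimate with no test attached. Whether time enters as a factor or as a number is not stated. Table 1 shows that the inter-session occasion is measured by EMA only, so the questionnaires, occupational balance among them, have three occasions: pre, post and follow-up.

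**The concern.** The null hypothesis implied for H1 to H3 is no benefit over the waiting list at post-training, and the claim needs both programmes to beat it. The null of the whole group × time test is that no arm differs from any other in its change at any occasion. These are different questions. Rejecting the second does not establish the first: it can come from follow-up alone, which belongs to H5, or from a single programme.

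With four procedures listed and none assigned to H1 to H4, the deciding result could be chosen after the data are seen. A programme with no post-training effect could be reported as confirming H1 to H3 because of follow-up. One effective programme could be reported as two. If the linear trend were used to decide, a benefit present at post and later lost could be reported as no effect.

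**Working it through.** **1. What was powered.** The protocol gives "small effect size (Cohen’s d^2^ = .08), to achieve a minimum of 80% power, a minimum sample size of 174 participants will be needed". For a within-between interaction, λ = N·m·f²/(1−ρ), df1 = (k−1)(m−1) and df2 = (N−k)(m−1). With k = 3 arms and m = 4 occasions, df1 = 6.
- d² = .08 gives d = 0.283 and f = d/2 = 0.141. With ρ = 0 and N = 174, λ = 174 × 4 × 0.02 = 13.92, df2 = 513, power 0.804.
- f = 0.10 with ρ = 0.5 gives the same λ and power.

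So 174 is reproduced as the size for a 6-df test of any difference in change among three arms over four occasions, under a correlation and f that the protocol does not state. It is not a calculation for a post-training contrast.

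**2. Common set-up for the illustrations.** From the protocol: 70 per arm, and pre, post and follow-up for the questionnaires. Assumed, because the protocol gives no figure: a benefit of 0.5 SD, equal correlations ρ = 0.5 between occasions (range 0.3 to 0.7), two-sided 5%, complete data, normal and chi-square approximations.

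**3. Pre-to-post contrast, one programme versus waiting list.** SE = √[2(1−ρ)·2/n] = √(2/70) = 0.169.
- Benefit at post: 0.5/0.169 = 2.96, power 0.84 (0.71 at ρ = 0.3; 0.97 at ρ = 0.7).
- Difference at follow-up only: the contrast is 0, rejection 0.05.

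**4. Whole group × time test (three arms, three occasions, 4 df).** If one or two of the three arms carry the same effect, λ = n × (2/3) × q, where q is the squared standardised effect on the two change scores. At ρ = 0.5 the change scores have variance 1 and covariance 0.5, so q = 0.25 × 4/3 = 1/3 both for a follow-up-only effect and for a maintained effect. Hence λ = 70 × 2/3 × 1/3 = 15.56.
- Both programmes differ at follow-up only: rejection 0.90 (0.77 at ρ = 0.3; 0.99 at ρ = 0.7), against 0.05 in step 3.
- Only MBHC-VR works, benefit kept: same λ, rejection 0.90. Both contrasts against the waiting list are significant in the right direction in about 2.5%, because the ineffective programme passes only by chance.
- With 56 per arm (70 × 0.8), λ = 12.44 and rejection is 0.82 in both cases.

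**5. Linear trend on the three-occasion questionnaires.** The weights are t minus the mean of t.

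| Time coding | Pre | Post | Follow-up |
|---|---|---|---|
| 0, 1, 2 | −1 | 0 | +1 |
| Weeks 0, 6, 18 | −8 | −2 | +10 |
| 0, 2, 3 (four-level scale, inter-session not observed) | −1.67 | +0.33 | +1.33 |

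For a contrast c, SE = √[(2/n)(1−ρ)Σc²]. For weeks 0, 6, 18, Σc² = 168 and SE = √(84 × 2/70) = 1.549. A post-only benefit gives −2 × 0.5 = −1, so z = −0.65. Rejection rates at 70 per arm, ρ = 0.5:

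| Pattern of 0.5 SD benefit | Trend 0, 1, 2 | Trend weeks 0, 6, 18 | Trend 0, 2, 3 | Pre-to-post contrast |
|---|---|---|---|---|
| Post only | 0.05 | 0.10 (slope of the wrong sign) | 0.10 | 0.84 |
| Follow-up only | 0.84 | 0.90 | 0.73 | 0.05 |
| Post, maintained | 0.84 | 0.73 | 0.90 | 0.84 |

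**The case against.** The protocol lists more than the interaction test. If time is a factor with pre and waiting list as references, the group × post coefficients are the pre-to-post contrasts wanted, and their Z-tests would answer H1 to H3. Changing the reference arm gives H4. The Tukey/Bonferroni comparisons could do the same, and would guard against reading one effective programme as two. The analysis section also uses the interaction to study trajectories and the persistence of differences, which is close to H5. An article may leave the choice of contrast to a fuller plan. All this shows that the right test is within reach, but the article assigns none of these procedures to H1 to H4. The one effect it does assign to H1 to H3, in the sample size section, is the interaction shared with H5.

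A reader might go further and infer that H1 to H4 are to be decided by a linear trend that ignores or penalises the post value. The document does not support that. The trend is described as a way to study the longitudinal course and is not named as the test of any hypothesis. The zero or negative weight depends on a time coding that is not stated, and other codings give a small positive weight. The large loss of power appears only if the benefit has faded by follow-up, whereas H5 expects it to last. For a maintained benefit the trend does about as well as the post contrast: 0.73 to 0.90 against 0.84.

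**Conclusion.** The point holds as a mismatch between hypothesis and test. H1 to H3 are fixed at post-training and claim that both programmes work. The test stated and powered for them has a null that spans all occasions and all arms. Under the illustrative 0.5 SD, the whole-effect test rejects in about 80 to 90% of trials (ρ = 0.5, 56 to 70 per arm) when the difference is at follow-up only or in one programme only. The tests that match the hypotheses reject in about 5% and 2.5% respectively. Those rates rest on the assumed effect, correlation and complete data; a smaller effect would shrink them, but the difference between the nulls does not depend on them. For H4 the gap is that no test is designated. The linear trend is a secondary matter: it is unsuitable for deciding a post-training hypothesis, and the protocol does not say that it will.

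**What to change.** In the Quantitative data analysis plan:
- State that time is categorical.
- Decide H1 to H3, for each outcome, by the model-based pre-to-post contrasts MBHC versus waiting list and MBHC-VR versus waiting list. Claim that both programmes improve only if both contrasts are significant.
- Decide the outcome part of H4 by the pre-to-post contrast MBHC-VR versus MBHC.
- Keep the whole group × time test and the linear trend as supportive results that do not decide H1 to H4.

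The model and data stay the same, and only wording changes, provided it is settled before the analysis. The price is that the joint claim is harder to reach than one omnibus p-value. With both programmes at 0.5 SD, ρ = 0.5 and 70 per arm, each contrast has power 0.84. The two share the waiting-list arm, so their statistics correlate at 0.5, and both are significant in about 0.75 of trials, against 0.90 for the omnibus test.

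### Cohen's d ignores baseline while Hypothesis 4 and the group x time test concern change, so the reported d is unbiased but less precise than the data allow and can disagree with the test

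*Protocol article*

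**What the plan says.** Three statements in the protocol article bear on this point.

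- **Hypotheses.** MBHC-VR, compared with MBHC, is expected to "result in greater magnitude of change in the occupational balance, mental health and psychological functioning variables (Hypothesis 4". The target is change.
- **Quantitative data analysis plan, the test.** "The group x time interaction will be used to study the trajectories of each group throughout the intervention". Pre-intervention is one of the levels of time, so this test uses baseline.
- **Quantitative data analysis plan, the effect size.** The rule is that "effect sizes (Cohen’s *d*) will be calculated by dividing the differences in means by the pooled standard deviation (SD"; it applies to the comparison of arms at the post-intervention and follow-up visits. The result is graded at 0.20, 0.50 and 0.80.

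The effect-size rule mentions neither change nor baseline adjustment, and does not say whether the means are observed or model-estimated. The only stated handling of baseline differences is by significance tests that "will be conducted to confirm that there were no demographic or clinical differences between groups at baseline".

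**The concern.** The hypothesis and the test are about change, whereas the statistic meant to express magnitude is about level at a later visit. The two can part company in the same results table.

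Two examples with observed values show this. If MBHC-VR happens to start 0.2 SD better than MBHC and both arms then improve equally, the difference in change is 0 but the rule gives d = 0.20, a small effect on the plan's own scale. If MBHC-VR starts 0.2 SD worse and gains 0.2 SD more, the difference in change is 0.20 but the rule gives d = 0.

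The sample size section rests on a small difference between MBHC with and without VR, so discrepancies of this order matter. The baseline significance tests do not guard against them. At 70 per arm a pairwise difference must reach about 1.96 x 0.169 = 0.33 SD to be significant, so an imbalance of 0.2 SD would pass unremarked.

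**Working it through.** **Inputs.** The sample size section gives alpha .05, 80% power, 174 participants (58 per arm), about 20% dropout, and 210 in total (70 per arm). Taking 20% from 210 leaves 168, or 56 per arm. The document gives no correlation rho between baseline and outcome, so rho is assumed to lie between 0.5 and 0.7.

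**The plan's own figure.** The plan gives no precision for d. Its nearest figure is the 174. For a three-group, four-time interaction, with f = 0.10 and a correlation of 0.5 between repeated measures, the noncentrality is N x 4 x 0.01 / 0.5 = 0.08N. At N = 174 this gives power 0.804, so 174 reproduces, but only with a correlation that the document does not state. Only the arm sizes are used below.

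**Step 1: the gap between d and the difference in change.** With both divided by the same SD:

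d(post) − d(change) = (difference at post) − (difference at post − difference at baseline) = difference at baseline.

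This holds in full, whatever rho is.

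**Step 2: size of the chance baseline difference.** In SD units its standard deviation is sqrt(2/n).

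| n per arm | SD of difference | P(above 0.20 SD) |
|---|---|---|
| 56 | 0.189 | 29% |
| 58 | 0.186 | 28% |
| 70 | 0.169 | 24% |

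The sample size section writes the effect as d squared = .08. Read literally, this is d = sqrt(.08) = 0.283, and an imbalance reaches that size in 9% of contrasts at 70 per arm and 13.5% at 56.

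**Step 3: how much of it is error against the true effect.** Only rho times the baseline difference carries into the post-intervention difference, so the carried part has SD rho x sqrt(2/n).

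| n per arm | rho | SD carried | P(above 0.20 SD) |
|---|---|---|---|
| 70 | 0.5 | 0.085 | 1.8% |
| 70 | 0.7 | 0.118 | 9.1% |
| 56 | 0.5 | 0.094 | 3.4% |
| 56 | 0.7 | 0.132 | 13.1% |

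**Step 4: bias.** In 20,000 simulated trials at 70 per arm with a true d of 0.20, the post-only d averaged 0.20, and so did the change-based d. Neither is biased.

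**Step 5: precision.** The standard errors are sqrt(2/n) for post-only d, sqrt(2/n) x sqrt(2(1 − rho)) for change, and sqrt(2/n) x sqrt(1 − rho²) with baseline adjustment. At 56 per arm:

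| rho | post-only | change | baseline-adjusted | variance cut, adjusted vs post-only (rho²) |
|---|---|---|---|---|
| 0.5 | 0.189 | 0.189 | 0.164 | 25% |
| 0.6 | 0.189 | 0.169 | 0.151 | 36% |
| 0.7 | 0.189 | 0.146 | 0.135 | 49% |

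A change-based d gains nothing at rho = 0.5 and loses below it (0.224 against 0.189 at rho = 0.3). The adjusted d is never worse than either.

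**Step 6: effect on the grading.** With no true effect and 56 per arm, |d| reaches 0.20 in 29% of contrasts by the written rule, against 22%, 19% and 14% after adjustment at rho = 0.5, 0.6 and 0.7. With a true d of 0.20 and rho = 0.6, the estimate has the wrong sign with probability Phi(−0.20/0.189) = 14.5% by the written rule and Phi(−0.20/0.151) = 9.3% after adjustment.

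**The case against.** The case against has several parts.

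- **The text does not say that the means are raw.** This is correct. The sentence sits in the multilevel-model section and could mean model-estimated means. The point survives, because a model with free group x time terms and no baseline covariate or constraint yields post-intervention means that still carry the baseline imbalance.
- **d is descriptive, and its time points are the planned ones.** The hypotheses are to be tested at post-training, and Hypothesis 5 at follow-up, which are the times at which d is computed. No decision rule uses d. This limits the consequence, but d remains the plan's stated measure of magnitude.
- **Randomisation already protects d.** It does protect against bias, as step 4 shows. It does not recover the lost precision or make d agree with the test.
- **The disagreement rate overstates the error in d.** At a true d of 0.20, d and the difference in change have opposite signs in 17–18% of contrasts at 56 per arm and 14–16% at 70. A reader might take that as the rate at which d is wrong. It is not, because the change score is noisy too: at 56 per arm and rho = 0.5 the conflicts split evenly (8.9% with post-only d wrong, 9.0% with change wrong).
- **Rewording the d sentence alone would not give agreement.** This stands. An adjusted d beside an unadjusted interaction would still differ in sign in 4.7–8.9% of contrasts, so the test has to come from the same contrast.
- **56 per arm counts completers only.** The plan is intention-to-treat with imputation, so 56 and 70 are best read as the two ends of a range.

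**Conclusion.** The point holds as a matter of precision and consistency. The stated effect size and the stated test answer different questions, and a baseline that is already collected goes unused in the former. The two differ by the chance baseline difference, with SD 0.17–0.19, exceeding 0.20 SD in 24–29% of pairwise contrasts at 70 down to 56 per arm. Adjustment would cut the variance of d by 25–49%, on the assumption that rho lies between 0.5 and 0.7.

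Three stronger readings are not supported. The rule does not bias d. An imbalance as large as the effect sought does not enter every effect size: it arises in a minority of contrasts, and the part that is error exceeds 0.20 SD in only about 2–13%. Nor is the MBHC-VR versus MBHC contrast less precise than the others, since with equal arms sqrt(2/n) applies to all three.

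**What to change.** Replace the effect-size rule along these lines: at post-intervention and at 3-month follow-up, d is the baseline-adjusted between-group difference from the multilevel model, divided by a named SD and given with a 95% confidence interval, for each pair of arms including MBHC-VR versus MBHC. The p-value for each difference is taken from that same contrast.

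Either form of adjustment will do. Baseline can enter as a covariate, in which case pre-intervention is no longer a level of time in the outcome model. Alternatively, pre-intervention stays as a level of time and the baseline means are constrained to be equal across the randomised arms.

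The cost is a small change to the model specification and the R code. It is more than one reworded sentence, because the model behind the test must change as well. No new data are needed, since baseline is already collected for every main outcome.
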